**Funder:**

National Institute for Health Research and Garfield Weston Foundation, Imperial College London

## 1. STUDY SUMMARY

Although therapeutic hypothermia for 72 hours reduces brain injury and improves long term neurodevelopmental outcomes after moderate or severe neonatal encephalopathy, the benefits and optimal duration of cooling therapy in mild encephalopathy is not known. Adverse neurodevelopmental outcomes at 2 years occur in 16% of babies with un-treated mild neonatal encephalopathy. In the phase I of the COMET trial, we have shown that it is feasible to identify and randomise babies with mild encephalopathy, and to obtain the primary outcome (proton MR spectroscopy levels of Thalamic N-acetyl Aspartate) accurately. The phase II of the COMET trial will examine the benefits and optimal duration of cooling therapy in babies with mild encephalopathy.

Currently, most centres in the UK routinely cool babies with mild encephalopathy, either knowingly or inadvertently. The former is primarily driven by a fear of legal implications of missing the therapeutic window, in case a baby with mild encephalopathy develops seizures after six of age and progress to moderate encephalopathy, while the latter is driven by a lack of awareness of the original cooling trial criteria and expertise in structured neurological examination in neonatal encephalopathy. A small minority of the UK centres accurately perform a neurological examination and aEEG within six hours of birth, and do not offer cooling therapy to babies with normal aEEG. Hence, the COMET trial will be conducted in two different cohorts, so that the key questions can be addressed in the most effective way with minimal disruption to the existing clinical practices of the recruiting sites.

### Research questions

1. Does whole body cooling initiated within 6 hours of birth and continued for 72 hours increase thalamic MR spectroscopy N-acetyl aspartate levels in babies with mild encephalopathy, when compared with those who are not cooled? (Cohort 1)
2. In babies with mild encephalopathy undergoing cooling therapy as clinical care, does rewarming at 48 hours as opposed to 72 hours result in similar thalamic N-acetyl aspartate levels? (Cohort 2)

### Study Population

**Cohort 1:** A total of 60 babies with mild encephalopathy ( $\geq 36$  weeks;  $\geq 2$  Kg) aged less than 6 hours will be recruited from several tertiary neonatal units in the UK, Europe, USA and Canada, over a 2 year period. The babies will be randomised to usual care (no cooling) or cooling therapy (core temperature 33 to 34 C) for 72 hours within six hours of birth. MR imaging and spectroscopy will be performed between 4 to 14 days after birth.

**Cohort 2:** A total of 80 babies with mild encephalopathy ( $\geq 36$  weeks;  $\geq 2$  Kg) aged 24 to 48 hours and undergoing cooling therapy as a part of standard clinical care will be recruited from several UK cooling centres, over a 2 year period. The babies will be randomised to rewarming after 48 hours or 72 hours of cooling therapy. MR imaging and spectroscopy will be performed between 4 to 14 days after birth. The babies recruited to cohort 1 will not be eligible for recruitment to cohort 2.

### Primary outcome (both cohorts)

- Proton MR spectroscopy Thalamic N-acetyl aspartate levels between 4 to 14 days of age.

### Benefits of the trial

These data will inform the national and international guidelines on management of babies with mild neonatal encephalopathy. If a shorter duration of cooling is as good or better than 3 days of cooling, this will reduce the intensive care stays, opioid use and separation from parents.

## 2. BACKGROUND

Birth asphyxia related brain injury (neonatal encephalopathy, NE) occurs in 4 to 6 per 1000 live births, and is the most common cause of death and neuro-disability in term babies in the UK. Moderate whole-body cooling, to a core temperature of 33.5°C for 72 hours, reduces death and disability after moderate or severe NE, and is used as the standard of care treatment for these babies across the NHS, and in other high-income countries. As these trials primarily focussed on babies with moderate or severe encephalopathy, the safety and efficacy of cooling therapy in babies with mild encephalopathy remains unknown. Two recent meta-analysis of cooling trials in babies with mild encephalopathy did not show any change in the clinical outcomes (death or moderate or severe disability) at 18 months, although the total number of babies included were too small to exclude a therapeutic effect.

### Brain injury and outcomes after mild encephalopathy

50% of affected babies with mild encephalopathy have brain injury on magnetic resonance (MR) imaging, and one third are reported to have an adverse long term neurodevelopmental outcome. Jacobs et al. (2011) reported adverse neurodevelopmental outcomes at two years of age in 8/24 (33%) children who had mild NE at birth and were not cooled. Murray et al. (2016) reported significantly lower full scale IQ, verbal IQ and performance IQ in 22 children following mild NE, when compared with 30 healthy controls, assessed at five years of age ( $p < 0.005$ ). Lally et al. (2014) have reported neurodevelopmental delays at 3.5 years of age in 8/24 (33%) south Indian babies with mild NE. Such neurodevelopmental impairments will have a profound lifelong impact, including an increased risk of autism^17, attention deficit disorders and learning difficulties.

The most accurate data on later outcomes after un-treated mild encephalopathy comes from the multicentre PRIME (Prospective research in mild encephalopathy) study. The PRIME study reported adverse neurodevelopmental outcomes at 2 years in 16% of babies with un-treated mild neonatal encephalopathy. Of these approximately 40% had severe adverse outcomes (Bayley III cognitive composite score  $< 70$ ; Gross motor function classification (GMFCS): 3 to 5) and 60% had mild adverse outcomes (Bayley III cognitive 70–84 or  $\geq 85$  and either GMFCS 1 or 2, seizures, or hearing deficit).

### Current practice of cooling therapy for mild encephalopathy

In the UK, a web based survey of 54 of the 68 UK cooling centres, reported that 36 (67%) routinely cooled babies with mild NE babies (who by definition do not meet the original cooling criteria). Although all centres used the same depth of cooling (33 to 34°C), the duration of cooling therapy varied widely – 39% discontinued cooling by 24h if there was a clinical improvement, and 61% cooled for the full 72h irrespective of clinical improvement. Separately, a recent audit of the London Neonatal Transport Service (NTS) reported a similar therapeutic drift, as 41% (59/145) of babies transported for cooling therapy in London had only mild or no NE. The situation in the USA is very similar. A survey in 2017, reported that all except 2 centres routinely offered cooling to babies with mild encephalopathy.

There are two key reasons for this therapeutic creep. Firstly, the NICHD neonatal research network cooling trial reported in 2005, used a standardised neurological examination without aEEG as the inclusion criteria for cooling. This criterion is extensively validated and accurately identifies babies with moderate and severe encephalopathy who are risk of adverse outcome, however it does require training and certification in the neurological examination.

Unfortunately, the TOBY trial published 4 years later, did not use a structured neurological examination, and instead mandated an abnormal aEEG for cooling. Hence, in the UK, most cooling centres never developed expertise in performing a structured NICHD neurological examination. When

cooling became the standard of care in the UK, most UK centres omitted aEEG as a cooling criterion and started offering cooling therapy based on an abnormal neurological examination alone. Without adequate training or certification in the NICHD neurological examination, most clinicians misclassify babies with mild encephalopathy as moderate and inadvertently cool babies these infants, despite most of them having a normal aEEG. In addition, many babies with perinatal asphyxia are transferred from peripheral hospitals to the cooling centres without an adequate neurological examination prior to initiation of cooling therapy. The clinicians at the cooling centres are then faced with a dilemma of continuing the therapy for full three days or discontinuing the therapy when the clinical picture is consistent with mild encephalopathy. Even when aEEG is used, clinicians are often unaware of the remarkably low specificity (less than 50%) of an early aEEG, and often mistake a moderate voltage abnormality in aEEG with moderate encephalopathy. Published data suggest that moderate or severe aEEG abnormalities can occur even in babies with mild encephalopathy, although it is unlikely that a baby with normal aEEG will have moderate or severe encephalopathy. Thus, clinicians offering cooling therapy to babies with normal aEEG are in fact cooling babies without encephalopathy or with mild encephalopathy.

Secondly, even if a structured neurological examination within six hours of birth is consistent with mild encephalopathy and aEEG is normal, a small proportion (approximately 5 to 10%) of these babies may develop seizures after six hours of age and progress to moderate or severe encephalopathy. This is because the brain injury following perinatal asphyxia evolves over the first 24 hours, and at present there are no effective ways of predicting which babies will worsen and develop seizures after six hours. Therefore, not initiating cooling therapy within six hours may be seen as a missed opportunity. Clinicians who are concerned about legal implications if these infants develop adverse outcomes later, tend to practice defensive medicine and offer cooling to any baby with abnormal neurological examination after perinatal asphyxia.

#### Preclinical data and the optimal duration of cooling therapy for mild encephalopathy

Preclinical models have consistently shown effective neuroprotection with cooling after moderate or severe NE , and more recently after mild NE . The brain injury evolves slowly after mild NE , and hypothermia is remarkably neuroprotective in such cases , when compared with severe brain injury . Hence it is possible that a shorter duration of cooling therapy would be sufficient to provide neuroprotection in mild NE.

However, the minimal duration of cooling for neuroprotection is species-dependent. Hence the optimal durations of therapeutic hypothermia in animal models and humans are different. For example, small animal models of NE (mice, rats) require shorter cooling durations and large animal models (pig, sheep) require longer cooling durations. Hence, most preclinical studies have observed neuroprotection with 24h to 48 h of cooling, while very short periods or very long periods of cooling are not neuroprotective .

Considering the rapid clinical recovery that occurs in mild NE, and the potential for over-ventilation and hypocarbia which could worsen brain injury, it is likely that these babies may benefit from a duration of cooling that is shorter than the full 72 hours. Such an approach would also reduce the length of intensive care stays and the need for prolonged sedation. Nevertheless, cooling for less than 24 hours is unlikely to be beneficial, and we have found MRI evidence of residual brain injury in 50% of the babies with mild encephalopathy who were cooled for less than 24, and long term adverse outcomes in 20% .

#### Safety and efficacy of cooling therapy in mild encephalopathy: meta-analysis.

We conducted a systematic review and meta-analysis of all cooling trials involving babies with mild neonatal encephalopathy (Figure 1). The pooled data including 117 babies with mild encephalopathy

showed an odd ratio of 1.12 (95% CI 0.42 to 2.98), and hence we need further evidence before recommending cooling as a standard therapy for these babies. Adverse neurodevelopmental outcomes at 18 months were seen in 20% of the babies with mild encephalopathy.

Figure 1. The effect of cooling on adverse outcomes (death, moderate or severe disability) after mild neonatal encephalopathy

[figure not shown]

### Surrogate MR biomarkers of long-term outcome in neonatal encephalopathy

An extensive systematic review and meta-analysis of the published literature suggested that MR spectroscopy biomarkers, measured shortly after birth, have the highest accuracy in predicting adverse outcomes years after neonatal encephalopathy. However, the published studies were based on single centre studies which are of limited use for multi-centre trials.

As a part of the MARBLE study we developed cross-platform MR spectroscopy techniques and prospectively examined the prognostic accuracy of various MR biomarkers in a multi-country setting. We found that the absolute concentration of thalamic N-acetylaspartate, [NAA], measured within two weeks of birth, had a near perfect 97% specificity and 100% sensitivity in predicting an adverse neurological outcome at 2 years after neonatal encephalopathy. Thalamic [NAA] at two weeks accounted for 40% of the variance observed in cognitive performance scores at two years of age, and significantly out-performed metabolite peak area ratios such as lactate/NAA, and other MR biomarkers including fractional anisotropy measurements.

### Brain injury after cooling therapy in babies with mild neonatal encephalopathy

We examined the brain injury in 41 babies with mild neonatal encephalopathy recruited into the MARBLE study. Of these, 27 babies were cooled for 72 hours ('full') and 14 were not cooled ('none') or were cooled for less than 6 hours ('partial'). Although the cooled babies were sicker, they had less white matter injury on conventional MR imaging and higher NAA/choline levels on MR spectroscopy.

Figure 2. Thalamic MR spectroscopy metabolites (left) and Bayley III composite scores (right) of cooled and non-cooled babies with mild encephalopathy.

[figure not shown]

### Justification of the COMET trial design

Given that the duration of cooling is species-dependent, it is unlikely that the optimal duration of cooling in animal models can be directly extrapolated to humans. The conventional approach of evaluating neuroprotective interventions in phase III trials is challenging in mild encephalopathy due to several reasons. For example, approximately 760 babies with mild encephalopathy need to be recruited per arm to detect a 30% reduction in the adverse outcomes (moderate or severe disability or death) at 80% power and 0.05% significance, given a control event rate of 20%. This requires a massive international effort and resources, and treatment failures at phase III trials are catastrophic. An alternative approach is to examine the mean differences in cognitive scores as an outcome measure. Such trials would still require large sample sizes and may not provide adequate information for health policy changes and the NICE guidelines.

In the COMET trial, we will use thalamic [NAA] as a surrogate biomarker to identify the benefits and optimal duration of cooling therapy in mild encephalopathy.

## **3. AIMS**

### Primary aims

1. To examine if whole body cooling initiated within 6 hours of birth and continued for 72 hours increase thalamic MR spectroscopy N-acetyl aspartate levels in babies with mild encephalopathy, when compared with those who are not cooled (Cohort 1)
2. To examine if, in babies with mild encephalopathy undergoing cooling therapy as clinical care, rewarming at 48 hours as opposed to 72 hours result in similar thalamic N-acetyl aspartate levels (Cohort 2)

### Secondary aims

1. To compare the brain injury on conventional MR imaging and peak area metabolite ratios of NAA/Creatine and NAA/Choline in cooled and non-cooled babies with mild encephalopathy.
2. To compare the brain injury on conventional MR imaging and peak area metabolite ratios of NAA/Creatine and NAA/Choline with 48 hours and 72 hours of cooling therapy in mild encephalopathy.
3. To compare the mean duration of hospital stay following no cooling, 48 hours and 72 hours of cooling therapy

4. To compare the host gene expression changes following no cooling, 48 hours and 72 hours of cooling therapy

#### 4. PATIENTS AND METHODS

All tertiary neonatal centres providing therapeutic hypothermia and with facilities for 3 Tesla or 1.5 Tesla MRI scanning and spectroscopy are eligible to participate in the COMET trial.

##### 4.1 Study participants

Babies (>35 weeks gestation and birth weight >1.8kg) requiring resuscitation at birth will be screened for eligibility and recruited if they meet the inclusion criteria. We will recruit a total of 140 term or near term (>35 weeks) babies (Cohort 1: 60 babies; Cohort 2: 80 babies) with mild neonatal encephalopathy over a 24 month period.

##### 4.2 Inclusion criteria

All of the following three criteria should be met:

**Cohort 1:** A total of 60 babies with mild encephalopathy ( $\geq 36$  weeks;  $\geq 2$ kg) aged less than 6 hours will be recruited from several tertiary neonatal units in the UK, Europe, USA and Canada, over a 2 year period. The babies will be randomised to usual care (no cooling) or cooling therapy (core temperature 33 to 34 C) for 72 hours within six hours of birth. MR imaging and spectroscopy will be performed between 4 to 14 days after birth.

##### Inclusion criteria

All of the following three criteria should be met:

1. Age less than six hours.  

AND
2. Evidence of acute perinatal asphyxia
  - a. Metabolic acidosis (pH <7.0 and/or BE >-16) in cord gas or a blood gas within one hour of birth.  

OR
  - b. If the pH or BE is borderline (pH <7.15 to 7.0) and/or BE >-10 to -16) in cord and/or blood gas within 1h of birth, or no blood gas available, additional evidence of perinatal asphyxia is required, which includes either an acute obstetric event (e.g. cord prolapse, abruption, shoulder dystocia) OR Need for continued resuscitation or ventilation at 10 minutes and/or a 10 min Apgar score <6  

AND
3. Evidence of mild encephalopathy (atleast two abnormalities) on the structured NICHD neurological examination performed between 1 and 6h of birth.

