## Appendix 1. NICHD Examination for neonatal encephalopathy

Eligibility criteria require  $\geq 2$  abnormal categories in mild and NOT  $\geq 3$  moderate or severe.

| CATEGORIES                         | NORMAL                                | MILD                                                                                                           | MODERATE                                  | SEVERE                                                          |
|------------------------------------|---------------------------------------|----------------------------------------------------------------------------------------------------------------|-------------------------------------------|-----------------------------------------------------------------|
| 1. Level of consciousness   | Alert, responsive to external stimuli | Hyper-alert, has a stare, jitteriness, high pitched cry, exaggerated response to minimal stimuli, inconsolable | Lethargic                                 | Stupor, Coma                                                    |
| 2. Spontaneous activity     | Normal                                | Decreased, with or without periods of excessive activity                                                       | Decreased                                 | No activity                                                     |
| 3. Posture                  | Predominantly flexed when quiet       | Mild flexion of distal joints (fingers, wrist)                                                                 | Strong distal flexion, complete extension | Intermittent decerebration                                      |
| 4. Tone                     | Strong flexor tone in all extremities | Slightly increased peripheral tone                                                                             | Hypotonia or Hypertonia                   | Flaccid or Rigid                                                |
| 5. Reflexes                 |                                       |                                                                                                                |                                           |                                                                 |

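### The base-excess limit in inclusion criterion 2a is reversed if read arithmetically, in both cohorts; the gestation, weight and examination wording also needs reconciling

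*Protocol*

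**What the plan says.** **Acidosis.** Protocol section 4.2 gives the same blood-gas test in the numbered inclusion lists of both cohorts. Criterion 2a is "Metabolic acidosis (pH <7.0 and/or BE >-16) in cord gas or a blood gas within one hour of birth". Criterion 2b begins "If the pH or BE is borderline (pH <7.15 to 7.0) and/or BE >-10 to -16". It then requires supporting evidence of asphyxia: an acute obstetric event, continuing resuscitation or ventilation at 10 minutes, or a low 10-minute Apgar score. The same requirement applies when no gas is available.

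**Gestation and weight.** Section 4.1 says "Babies (>35 weeks gestation and birth weight >1.8kg) requiring resuscitation at birth will be screened for eligibility", with recruitment conditional on the inclusion criteria. Its next sentence says "We will recruit a total of 140 term or near term (>35 weeks) babies". The study population text in section 1 and the cohort paragraphs in section 4.2 give at least 36 weeks and at least 2 kg for both cohorts. Neither numbered list contains a gestation or weight item.

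**Examination.** Cohort 1 criterion 3 is "Evidence of mild encephalopathy (atleast two abnormalities) on the structured NICHD neurological examination performed between 1 and 6h of birth". Appendix 1 states the eligibility rule as at least two "abnormal categories in mild and NOT" three or more moderate or severe. The Cohort 2 numbered list has no examination item, although the Cohort 2 paragraph in section 4.2 requires the examination before randomisation.

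**The concern.** BE becomes more negative as acidosis worsens, so a limit meant to identify severe acidosis should catch values below -16. As printed, the inequality catches values above it. Because it is joined to the pH limit by and/or, the BE limb is sufficient alone.

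Section 10 rules out enrolling a baby who misses any eligibility criterion, which makes the printed criteria the compliance standard. Section 4.3 makes randomisation web-based, and Cohort 1 is to recruit in the UK, Europe, the USA and Canada. A limit copied literally into an electronic check could let through babies without metabolic acidosis and turn away some with the most negative BE. A monitor working from the printed text could also record a correct enrolment as a breach.

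The gestation, weight and examination statements raise a smaller question of the same kind: two sections describe one eligibility rule differently, and the numbered lists do not settle it.

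**Working it through.** The protocol gives no figure to reproduce here. The check is one of logic, applied to the wording of section 4.2.

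**1. Criterion 2a, as printed and with the inequality reversed**

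- As printed: pH < 7.0 or BE > -16.
- Reversed: pH < 7.0 or BE < -16.
- Borderline band in 2b, read as a range: 7.0 ≤ pH < 7.15, or -16 ≤ BE < -10.

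The pH and BE pairs below are illustrations chosen to fall in each region.

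| pH | BE | 2a as printed | 2a reversed | In 2b band |
|---|---|---|---|---|
| 7.30 | -2 | met | not met | no |
| 7.20 | -8 | met | not met | no |
| 7.20 | -12 | met | not met | yes, on BE |
| 7.10 | -12 | met | not met | yes, on both |
| 7.10 | -18 | not met | met | yes, on pH |
| 7.20 | -20 | not met | met | no |
| 6.95 | -18 | met, on pH | met | no |

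Three results follow.

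- A baby with pH 7.30 and BE -2, who has no metabolic acidosis, meets 2a as printed.
- A baby with pH 7.20 and BE -20 fails 2a as printed and lies outside the 2b band, so a measured gas of this kind has no route to eligibility.
- Every BE above -16 and up to -10 already satisfies 2a as printed (for example, -12 > -16). The supporting-evidence rule for a borderline BE is left with only the single value -16.

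With the inequality reversed, the two BE bands no longer overlap. The pair 7.20/-12 falls only in 2b and needs supporting evidence, while 7.20/-20 meets 2a.

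**2. Gestation and weight**

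- Weight: birth weights above 1.8 kg and below 2 kg fall inside the section 4.1 screening range and outside sections 1 and 4.2.
- Gestation: counted in days, above 35 weeks includes 35+1 to 35+6, which sections 1 and 4.2 exclude. Counted in completed weeks, above 35 is the same as at least 36 and there is no gap.

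**3. Examination unit**

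Appendix 1 has six categories. Four have one item each, reflexes has two (suck, Moro) and the autonomic category has three (pupils, heart rate, respirations), so there are 4 + 2 + 3 = 9 items. The number of two-item patterns is 9 × 8 / 2 = 36. Pairs within one category number 1 (reflexes) + 3 (autonomic) = 4. In those 4 of 36 patterns, for example tachycardia with hyperventilation, a baby has two abnormal items but one abnormal category. These are counts of patterns, not proportions of babies.

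**The case against.** The strongest reply is that this is a slip of notation whose meaning can be recovered. Criterion 2a is labelled metabolic acidosis and paired with a low pH. Criterion 2b runs from less to more acidotic on both scales, and its own BE band makes no sense arithmetically, since values between -10 and -16 are not above -10. Treating the sign > as a larger deficit is the only reading under which 2a and 2b both work. That stands, and it limits the practical risk. It does not make the printed limit correct, because section 10 holds sites to the written criteria.

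Other checks also limit the harm. Cohort 1 requires mild encephalopathy on a structured examination and excludes babies who have none. Cohort 2 requires cooling continued beyond 24 hours by the clinical team, an examination, and central review where eligibility is in doubt. This stands too, with one qualification: the Cohort 2 numbered lists contain neither an examination threshold nor an exclusion for absence of encephalopathy.

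On gestation and weight, the 1.8 kg figure appears only in a screening sentence that defers to the inclusion criteria, and a screening range may be wider than the eligible range. A reader might infer that a 1.9 kg baby is eligible because no numbered item excludes it. The documents do not support that, since the 2 kg limit is stated for both cohorts within section 4.2. What remains is the 35-week figure repeated for recruited babies, and the absence of both limits from the numbered lists.

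On the examination, a reader might infer that the two thresholds conflict. Both require at least two, and Appendix 1 supplies the unit that criterion 3 leaves loose. Only the inconsistent unit remains.

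**Conclusion.** The point holds as a wording error in a binding eligibility criterion. Criterion 2a, identical in both cohorts, has its BE inequality reversed if read arithmetically. So read, it is met without metabolic acidosis, is not met by BE below -16 when pH is 7.0 or above, and empties 2b's rule for a borderline BE of almost all effect. The intended direction can be inferred, so the risk lies in literal use: an eligibility form, the web-based randomisation check or monitoring. Those forms are not in the document, so whether they carry the error is unknown.

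A reader might go further and infer that unintended babies will be enrolled, diluting the Cohort 1 effect, costing power and favouring similarity in Cohort 2. The document does not support that. It gives no effect size, standard deviation or power for thalamic NAA, and no basis for the proportion of babies who might enter wrongly. No size can be put on such an effect, and none is claimed.

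The gestation and weight discrepancy is real but minor, and its gestation part depends on how weeks are counted. The examination wording is a matter of consistency only.

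**What to change.** 1. In both numbered lists of section 4.2, restate 2a and 2b as base deficit, or correct the inequality, so that on BE they form separate, ordered bands, with 2a the more acidotic. State which band a value exactly at the boundary belongs to.
2. Check the eligibility form, the web-based randomisation check and any monitoring checklist against the restated criteria.
3. Reconcile section 4.1 with sections 1 and 4.2 on gestation and weight, say whether gestation is counted in completed weeks, and enter the agreed limits as an item in both numbered lists.
4. Use one counting unit, abnormality or category, in criterion 3 and Appendix 1.

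Which limits apply is for the sponsor to decide. The cost is a wording amendment and a check of the forms; sample size, outcomes and visit timing are unaffected.
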